#### Clinical data

In addition to PROs, clinical data regarding patient and tumor characteristics, as well as treatment information, is needed to meet our research objectives. These data are extracted from the Netherlands Cancer Registry (NCR). Maintained by the Netherlands Comprehensive Cancer Organisation (IKNL), the NCR is a nationwide population-based registry that contains information on all newly diagnosed cancer patients in the Netherlands. Clinical data are retrieved from patients electronic health records in the hospitals by well-trained, independent data managers of the NCR. The standard data collection in the NCR is expanded for patients included in this study and includes patient characteristics (i.e. age, height, weight, comorbidities), tumor characteristics (i.e. TNM staging, PSA at diagnosis and Gleason grade on biopsy and prostatectomy if applicable), diagnostic procedures (i.e. imaging, biopsy technique, pelvic lymph node dissection) and treatment information for prostatectomy (i.e. nerve sparing procedure, positive margins, complications) and EBRT (i.e. type of radiotherapy, dose per fraction, integrated/brachytherapy boost, toxicity). In addition, data is collected on all post-treatment PSA measurements, disease progression, subsequent treatments and cause of death until 5 years after diagnosis. Vital status of all patients is updated annually by linkage to the personal records database (BRP) which contains data on the vital status, date of death and emigration status of all Dutch citizens.

Moreover, additional clinical data related to volumes of care are collected from the electronic health records to evaluate healthcare costs. In addition to the treatments for prostate cancer, these data include treatments for adverse events, consultations with medical specialists, hospitalizations and medication use.

### Statistical analysis and sample size

Descriptive analyses will be used to provide insight in patient and clinical characteristics of the total study population and of both treatment groups. Mixed-effects models will be used to compare functional outcomes and HRQoL between the two treatment groups over time. Differences in functional outcomes and HRQoL between treatment modalities as measured by the EPIC-26 will be considered clinically meaningful if they are equivalent to or exceed the MCID and are statistically significant at the 0.05 level. The p-value maintained for statistical significance will be adjusted for multiple testing if appropriate. For the EORTC-QLQ-C30, the between-group anchor-based minimally important differences per scale as reported by Musoro et al. will be used to compare treatment groups over time. For scales for which no anchor-based estimates are available, distribution-based estimates will be used [25]. Due to the observational design of the study, we will adjust for confounding covariates associated with treatment with RARP versus EBRT (and ADT) using inverse probability of treatment weighting or the g-formula [30–33]. In case of missing values in covariates, multiple imputation procedures will be used [34, 35]. Competing risk survival analyses will be used to evaluate PFS and DMFS with the competing event being a non-PCa related death.

To evaluate incremental cost-effectiveness of EBRT combined with ADT versus RARP over a time horizon of 36 months, a cost-utility analysis (CUA) will be conducted both from a societal and a medical perspective. Costs are assessed by multiplying the voluminal with the unit prices. Utilities will be derived by means of a mapping algorithm from the EORTC QLQ-C30 at each time point. The derived utility will be used for the estimation of a quality adjusted life year (QALY) according to the trapezium rule. Incremental costs between treatments will be related to incremental QALYs in a cost-utility ratio (ICUR) to determine the additional costs that need to be spent to gain one QALY. Subsequently, a budget impact analysis (BIA) will be performed to predict the financial consequences related to the adaption and implementation of the favored strategy based on the cost-effectiveness analysis.

Assuming that the effect of treatment on HRQoL is predominantly determined by functional outcomes, the sample size was calculated to demonstrate the mean or upper limit of the MCID-range for each domain of the EPIC-26. A two sided T-test (alpha = 0.05, power 80%) using expected standard deviations, derived from previous research evaluating the impact of RP versus EBRT and ADT on functional outcomes, yielded a required total response of 471 patients at T36 [12]. To account for confounding factors, the sample size was increased by 15%. Based on previous experience with collecting PROs, we assume that 75% of men who are willing to participate in the study and complete the baseline questionnaire will do so again at each subsequent measurement moment. Therefore, 837 patients need to be included in the study (response at T0) for sufficient power.

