**Methods:**

The RECOVER study is a comparative effectiveness study that prospectively includes newly diagnosed high-risk (cT3a-bN0M0, ISUP-grade ≥ 4 and/or PSA > 20 ng/mL), non-metastatic PCa patients. Four Dutch prostate cancer networks, comprising 29 hospitals, are currently participating in the study. Patient reported outcomes are collected before treatment initiation, 12 months and 36 months after treatment initiation and include the EORTC-QLQ-C30, the EPIC-26, an adapted version of the SCQ, an adapted version of the iMTA Productivity Cost Questionnaire and several specific questions regarding patient characteristics, treatment of PCa specific complaints and health resources used. Clinical data regarding patient-, tumor- and treatment characteristics and oncological outcomes are collected up to 5 years after diagnosis. For sufficient power, patient reported outcomes of 471 patients must be collected 36 months after treatment initiation. Descriptive statistics and mixed-effects models are used to assess differences in HRQoL and functional outcomes over time between the patients treated with radical prostatectomy versus EBRT (+ ADT). Inverse probability of treatment weighting or the g-formula are used to adjust for confounding covariates associated with treatment. Secondary endpoints PFS and DMFS are evaluated using a competing risk analysis and cost-utility and budget-impact analyses will be performed to determine cost and cost-effectiveness.

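### The sample size steps do not produce their total: 837 is 471 divided by retention alone, so the text leaves unclear whether the 15% allowance for confounding is in the target

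*Protocol article*

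**What the plan says.** The derivation is in the last paragraph of Methods, Statistical analysis and sample size, and runs in this order:

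1. The method is "A two sided T-test (alpha = 0.05, power 80%) using expected standard deviations" taken from earlier research. The target difference is described thus: "the sample size was calculated to demonstrate the mean or upper limit of the MCID-range for each domain of the EPIC-26".
2. This calculation "yielded a required total response of 471 patients at T36".
3. "To account for confounding factors, the sample size was increased by 15" per cent.
4. It is assumed that 75% of men who "complete the baseline questionnaire will do so again at each subsequent measurement moment".
5. "Therefore, 837 patients need to be included in the study (response at T0) for sufficient power".

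The Methods part of the Abstract repeats the 36-month figure as the requirement: "For sufficient power, patient reported outcomes of 471 patients must be collected 36 months after treatment initiation". It also gives the schedule: "Patient reported outcomes are collected before treatment initiation, 12 months and 36 months after treatment initiation". Table 1 has the same two follow-up points, T12 and T36. The only sample sizes printed anywhere are 471 and 837.

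**The concern.** Read in order, the paragraph starts from a t-test result of 471, raises it by 15%, allows for non-response and arrives at 837. If that were so, 837 would exceed what non-response alone requires. It does not, so one of the printed statements must be wrong.

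The step matters because the comparison is not randomised. The article commits to inverse probability of treatment weighting or the g-formula, and the 15% is the only provision it states for the cost of that adjustment. The baseline target, the 36-month target in the Abstract and the 80% power claim all depend on where the 15% sits. At the time of the article (January 2025) 340 patients had been included and accrual was expected to finish by 2026, so the target was still open.

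**Working it through.** **Inputs, all from the protocol article.** Two-sided alpha 0.05 and power 80%; 471 at T36; a 15% increase; 75% retention at each later measurement (Statistical analysis and sample size). Two later measurements, T12 and T36 (Abstract, Methods; Table 1).

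**Step 1: reproduce 837.** Cumulative retention to T36 is 0.75² = 0.5625.
- 471 / 0.5625 = 837.3
- 837 × 0.5625 = 470.8

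The figure is reproduced from 471 and retention only.

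**Step 2: apply the 15% where the text puts it.**
- T36: 471 × 1.15 = 541.65, so 542
- T0: 541.65 / 0.5625 = 962.9, or 542 / 0.5625 = 963.6, so 963–964
- Difference from 837: 126–127 patients

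**Step 3: try other readings.**

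| Reading | T0 |
|---|---|
| One 75% step, no 15% | 471 / 0.75 = 628 |
| One 75% step, with 15% | 541.65 / 0.75 = 722 |
| 15% taken as division by 0.85, two steps | 471 / 0.85 / 0.5625 = 985 |
| 15%, and 25% added twice | 471 × 1.15 × 1.25² = 846 |

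The last comes nearest but misses by 9, and adding 25% twice is not the same as 75% retention. None of these gives 837.

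**Step 4: the reading in which 471 already contains the 15%.** 471 / 1.15 = 409.6. Forwards, 409 × 1.15 = 470.4 and 410 × 1.15 = 471.5, so a t-test result of about 410 leads to 471 and then to 837. All the printed numbers fit; the statement that the t-test gave 471 does not.

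**Step 5: the reading in which 471 is the raw t-test number.** Suppose adjustment costs the budgeted 15%. The effective number at T36 is 471 / 1.15 = 409.6. With the standardised difference fixed so that 471 gives 80% power (1.960 + 0.842 = 2.802):

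Power = Φ(2.802 × √(409.6/471) − 1.960) = Φ(2.802 × 0.9325 − 1.960) = Φ(0.653) = 0.743

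The noncentral t gives the same 74.3% at 1:1 and at 2:1 allocation. This relative calculation does not need the standard deviations.

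**Step 6: can the article decide between them?** Recomputing 471 or 410 from first principles would need the standard deviations, the value taken from each domain's range of clinically important differences (mean or upper limit) and the allocation ratio. None is printed.

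**The case against.** The strongest reply is that this is a condensed article in which only the final 36-month figure is printed and the allowance is mentioned afterwards. On that view about 410 became 471 and 471 became 837, and nothing is wrong beyond sentence order and one verb. The Abstract supports this, since it presents 471 as the number to be collected at 36 months and no larger T36 figure appears anywhere. This stands as a plausible explanation. It does not make the paragraph correct, because the t-test would then not have produced 471.

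A reader might go further and infer that the 15% is in neither 471 nor 837, so that the study is underpowered. The article does not show that: Step 4 gives a reading in which both numbers contain it.

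A reader might also take 74% as the actual power. It is conditional twice over. It needs 471 to be uninflated, and it needs adjustment to cost exactly 15% with no gain elsewhere. The plan is for mixed-effects models with outcomes at baseline, T12 and T36, whereas the sizing is a plain t-test, so use of the baseline score could recover precision. As an illustration, under an assumed baseline-to-T36 correlation ρ that multiplies the variance by 1 − ρ², 80% power is restored when 1.15 × (1 − ρ²) = 1, that is ρ ≈ 0.36. The article gives no correlation, so this shows only that an offset is possible.

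Finally, a reader might ask whether 15% is enough for weighting. That is a separate question. The article gives no propensity model or allocation ratio, and it leaves open the g-formula, which uses no weights.

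**Conclusion.** The inconsistency is established by the article's own figures: 837 equals 471/0.75² to rounding, and the 15% increase is not applied between the two. Applied as written, it would require about 542 at T36 and 963–964 at T0.

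Which statement is wrong is not established. If 471 already includes the 15%, the target and the 80% power stand and the error is one of description. If 471 is the raw t-test number, the target carries no allowance for confounding and power is about 74%, on the assumptions that adjustment costs the budgeted 15% and that nothing offsets it. The 74% is a conditional figure and not a demonstrated loss. The point still needs correcting, because a sample size on which the study relies cannot be derived from its stated steps.

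**What to change.** Check the original calculation, then print three numbers as separate steps: the t-test result, the number at T36 after the 15%, and the number at T0 after 75% retention at each of two measurements.

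- **If 471 already includes the 15%:** say that the t-test gave about 410 (the exact figure from the original calculation), that the 15% raised it to 471 at T36, and that retention gives 837 at T0. The 837 stays as it is.
- **If the 15% was omitted:** keep 471 as the t-test result, say that 837 contains no allowance for confounding, and restate the power as about 74% under the 15% assumption.

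The cost is one corrected paragraph, with the Abstract's sentence on 471 checked against it. The correction itself requires no additional enrolment. In the second case the stated power becomes less favourable.

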### Patient and public involvement

The Dutch Prostate Cancer Foundation (Prostaatkankerstichting, [PKS]) was involved in the design of this study. A patient representative of the foundation is part of the RECOVER study steering committee and therefore involved throughout the whole study. Next to this, PKS facilitates the communication of study-related information and research findings via their channels to patients.

### Ethical approval and consent to participate

The Medical Research Ethics Committee Oost-Nederland declared that the study is not subject to the Medical Research involving Human Subjects Act and Medical Treatment Contracts Act in June 2022 (2022–13682). An informed consent is filled out by all patients willing to participate in the study. Moreover, this study was approved by the Privacy Review Board of the NCR (k23.0170).

## Results

### Start-up and patient accrual

Patient recruitment is set up in a step-wise fashion; patient accrual started in February 2023 in the first prostate cancer network (including 3 hospitals), followed by the second network (6 hospitals) in June 2023. The third network (8 hospitals) started patient accrual in October 2023 and the final network (11 hospitals) started in January 2024. The study might be expanded toadditional hospitals during the inclusion period. An up-to-date overview of the participating hospitals is accessible from ClinicalTrials.gov [17]. We anticipate that patient accrual will be completed by 2026, collection of PROs will be finalized by 2029 and collection of clinical follow-up data by 2031. Currently (January 2025), 4 prostate cancer networks and 340 patients participate in the RECOVER study.

## Discussion

RARP and EBRT (often combined with ADT) are frequently used treatment modalities for high-risk, non-metastatic PCa. Research is needed to provide further insight into differences in functional outcomes, HRQoL, oncological outcomes and costs. By evaluating and comparing both treatments we aim to enhance patients’ and healthcare professionals’ awareness regarding the impact of both treatment modalities and aid treatment decision making. Moreover, our results could contribute to a reduction in inter-hospital and inter-physician variability and an improvement in the quality of care, facilitated by the adjustment and/or refinement of treatment recommendations concerning this patient population in (inter)national guidelines.

When designing the RECOVER study, a prospective observational design was purposely chosen over a randomized controlled trial. Randomized controlled trials are the mainstay and gold standard for efficacy studies as they can provide compelling evidence for cause-effect relationships, have the potential for great internal validity and minimize confounding. Patient accrual, however, has shown to be difficult for trials randomizing over surgical and radiation based treatment arms for PCa [36–38]. Both patients and their treating physicians often have a preference for treatment with RARP or EBRT and patients do not want to be randomly assigned to a treatment [36, 39]. As low patient accrual can lead to early termination of the study and consequently no or inconclusive results, a RCT was not deemed feasible. A prospective comparative effectiveness cohort study is the next best alternative to compare RARP and EBRT [40, 41]. Observational study designs evaluate effectiveness of treatment rather than efficacy, are more ethically feasible, reflect daily practice more closely and therefore have good generalizability and can enroll more patients due to lower costs [42, 43]. This enhances statistical power and enables the possibility to generalize results to the high-risk, non-metastatic PCa patient population at large [43]. A limitation of observational studies is the risk of confounding. We aim to improve comparability between both treatment groups by means of the inclusion criteria (e.g. age, performance status). Furthermore, detailed information regarding possible confounding factors will be collected in both our clinical data and questionnaires. In our analyses, measured baseline covariates are balanced across treatment groups with inverse probability of treatment weighting or by covariate adjustment using the g-formula to create comparable populations.

Through its pragmatic design, the RECOVER study accommodates variability in current clinical practice. Surgical treatment may be part of a multimodal strategy with (neo)adjuvant ADT and/or adjuvant radiotherapy. Variation in the RARP group is expected to be limited as (neo)adjuvant ADT is not commonly applied in the Netherlands and early salvage radiotherapy is often preferred over adjuvant radiotherapy even for pN1 disease. In current clinical practice, most patients treated with EBRT (> 90%) receive adjuvant ADT with a LHRH agonist for the duration of 6 to 36 months. In a recent Dutch consensus meeting, the duration of ADT for high-risk PCa was proposed to be 6 to 24 months depending on tumor characteristics.

Besides QoL-related and oncological endpoints, our study will provide insight into the costs and cost-effectiveness of both treatment modalities. Costs of healthcare have been rising substantially over the past decades. A significant proportion of these costs is directed at cancer care, of which prostate cancer is indicated as one of the priciest cancers [44]. In order to control the rising healthcare expenses, it is important to consider costs and cost-effectiveness of treatment. Only few studies have been performed regarding the costs of RP and EBRT for high-risk, non-metastatic PCa and these studies mostly focused on the American or Canadian health care system. This study will provide insight into the cost and cost-effectiveness of care for high-risk, non-metastatic PCa from a Dutch societal and medical perspective.

Altogether, we aim to provide insight into the effects of treatment with RARP versus EBRT combined with ADT from a multidimensional view, including functional outcomes, HRQoL, PFS, DMFS and cost-effectiveness. Thereby we aim to create opportunities for the improvement of quality of life and quality of care for patients with high-risk, non-metastatic PCa.

## Data Availability

No datasets were generated or analysed during the current study.

## Abbreviations

ADT: Androgen deprivation therapy
ARSI: Androgen receptor signaling inhibitor
ARTA: Androgen receptor targeted agents
BED: Biologically effective dose
BIA: Budget impact analysis
BRP: Personal records database
CTCAE: Common toxicity criteria for adverse events
CUA: Cost-utility analysis
DMFS: Distant metastasis free survival
DRE: Digital rectal examination
EBRT: External beam radiation therapy
EORTC-QLQ-C30: European Organization for Research and Treatment of Cancer Quality of Life Questionnaire-C30
EPIC-26: Expanded prostate cancer index composite-26
HDR: High dose rate
HRQoL: Heath-related quality of life
ICUR: Incremental cost-utility ratio
IKNL: Netherlands Comprehensive Cancer Organisation
IMRT: Intensity modulated radiation therapy
iMTA: Institute for medical technology assessment
LDR: Low dose rate
MDTM: Multidisciplinary team meetings
MREC: Medical review ethics committee
MRI: Magnetic resonance imaging
NCR: Netherlands Cancer Registry
NVRO: Dutch Society of Radiotherapy and Oncology
NVU: Dutch Association for Urology
OS: Overall survival
PCa: Prostate cancer
PCSM: Prostate cancer-specific mortality
PCSS: Prostate cancer-specific survival
PCQ: Productivity cost questionnaire
PFS: Progression-free survival
PKS: Dutch PCa patient foundation
PLND: Pelvic lymph node dissection
PROFILES: Patient reported outcomes following initial treatment and long term evaluation
PROs: Patient reported outcomes
PROMs: Patient reported outcomes measures
PSA: Prostate specific antigen
RARP: Robot-assisted radical prostatectomy
RECOVER: High-Risk prostatE Cancer radiatiOn Versus surgERy
RP: Radical prostatectomy
SCQ: Self-administered comorbidity questionnaire
VMAT: Volumetric modulated arc therapy
QALY: Quality adjusted life year
